## Abstract

**Background:**

Stroke is a significant public health concern that causes severe and long-lasting disability. The recurrence of stroke is increasing due to lack of patients’ knowledge and compliance with treatment to control modifiable risk factors and lifestyle changes. Health education can be an effective way to increase knowledge about behavioral changes in patients who had a stroke.

**Objective:**

The aim of this study is to evaluate the effectiveness of a health education program in Bangladesh for patients who had their first stroke and their family caregivers in order to reduce the recurrence of stroke by controlling modifiable risk factors.

**Methods:**

This is a parallel, open-label, prospective randomized controlled trial conducted at the National Institute of Neurosciences & Hospital in Dhaka, Bangladesh. We enrolled ≥18-year-old patients of both sexes who had a history of first stroke attack (transient ischemic attack, hemorrhagic stroke, lacunar stroke, atherothrombotic stroke, or cardioembolic stroke). We stratified patients into those aged <65 years and those aged ≥65 years and according to types of strokes for randomization. Our estimated sample size was 432. The intervention group receives face-to-face counseling on lifestyle modifications, blood pressure monitoring, and medication compliance–related health education during enrollment and monthly follow-ups. However, the control group receives only usual care from the hospital. The primary end point of this study is the reduction in the stroke recurrence rates at the end of the 12-month follow-up period. The secondary end points are to (1) assess the occurrence of all adverse events such as other cardiac events and all-cause mortality, (2) evaluate the status of the controlling modifiable risk factors such as blood pressure, glycated hemoglobin, and non–high-density lipoprotein cholesterol, (3) assess the knowledge related to stroke by using the investigator-developed questionnaire, (4) evaluate the lifestyle behavior related to stroke by using the investigator-developed questionnaire, (5) assess medication adherence, and (6) evaluate the quality of life of patients who had a stroke and their family caregivers. The evaluation points will be at baseline, 6 months, and 12 months for both groups.

**Results:**

Patients’ enrollment started on October 2022, and follow-up will be completed in March 2024. A total of 432 participants were included in both the intervention (n=216) and control groups (n=216). This study was approved by the institutional review board and the ethics review board of the National Institute of Neurosciences & Hospital (IRB/NINSH/2022/151) on August 30, 2022.

**Conclusions:**

Our health education program is expected to reduce the recurrence of stroke and improve the quality of life of patients who have had the first stroke. The results of this study will provide insights into the importance of health education for (self)-management and prevention of stroke.

**Trial Registration:**

ClinicalTrials.gov NCT05520034; https://clinicaltrials.gov/ct2/show/NCT05520034

**International Registered Report Identifier (IRRID):**

DERR1-10.2196/51178

## Introduction

### Background

Stroke is a major global health concern, ranked as the second highest cause of death in 2019 [1], with an estimate of 93.2-110.5 million people affected worldwide [2]. This debilitating condition causes long-term physical, mental, and social disability, leading to financial difficulties for patients and their families [2,3]. People are affected by stroke in both low-income and high-income countries, and most cases have been reported in older age groups [4,5], although it has also been reported in younger individuals, especially in low-income countries [6]. In 2019, the burden of stroke increased from 70% to 85% between 1990 and 2019, and the mortality rates rose by 43% during this period. Among them, 62.4% experienced an ischemic stroke, 27.9% had an intracerebral hemorrhage, and 9.7% had subarachnoid hemorrhage, with corresponding mortality rates of 4%, 0.36%, and 0.36%, respectively, resulting in a total death rate of 6% [2]. A meta-analysis of 26 studies from 1997 to 2019 found stroke recurrence rates ranging from 5.7% to 51.3% over 1-10 years, with a 1-year recurrence rate of 5.7%-17.7% [7]. The first 3 months following the initial attack are the most critical for recurrence [8]. Moreover, the meta-analysis indicated that factors such as diabetes mellitus, smoking status, peripheral artery disease, hypercoagulable state, depression, 24-hour minimum systolic blood pressure (BP), 24-hour maximum diastolic BP, age, family history of stroke, National Institutes of Health Stroke Scale score status, hypertension, and history of cardiac disease were found to influence the recurrence of stroke [9,10].

In Bangladesh, stroke is the topmost cause of death, accounting for 82.31 deaths per 100,000 people in 2019 across all age groups and genders [11], with prevalence of approximately 11.39 cases per 1000 people [4]. Among them, 79.7% experienced ischemic stroke, 15.7% had hemorrhagic stroke, and 4.6% were diagnosed with subarachnoid hemorrhage [4]. A hospital-based study in Bangladesh reported cumulative recurrence rates of 14.7% at 3 months, 15.3% at 6 months, 17.3% at 9 months, and 20% at 1 year, predominantly in individuals older than 75 years [8]. Male patients with hypertension, diabetes, and dyslipidemia had a higher risk of recurrence compared to females. Additional risk factors included hypertension (79.2%), dyslipidemia (38.9%), tobacco use and smoking (37.2%), diabetes (28.8%), ischemic heart disease (20.1%), atrial fibrillation (13.9%), and obesity (9.7%) [4].

Secondary preventive measures must be implemented that address comorbidities such as hypertension and diabetes through lifestyle modifications, surgical interventions, and pharmacological interventions to reduce the recurrence of stroke [12]. Health education interventions can effectively enhance knowledge, raise awareness, modify lifestyle behaviors, and control modifiable risk factors, ultimately improving the quality of life (QoL). A study demonstrated that a 6-month health education program reduced stroke recurrence rate by 50% at 30-month follow-up [13]. Furthermore, regular postdischarge checkups and early follow-ups are necessary to prevent complications and further recurrence. Many countries worldwide have implemented stroke prevention efforts [14]. A randomized controlled study showed that both face-to-face and telehealth education programs resulted in significant improvements in health behaviors related to physical activity, nutrition, low-salt diets, and medication adherence. Additionally, the intervention group exhibited decreased systolic BP and cholesterol levels [15,16]. Another similar study using a randomized controlled design found that a web-based stroke education program led to significant increases in exercise, reduced consumption of salty foods, increased intake of fruits and vegetables, enhanced sense of control, improved health motivation, and improved caregiver mastery. However, all these interventions did not result in significant reduction of stroke recurrence [17]. In Bangladesh, a significant challenge for patients who have had a stroke is the absence of a follow-up system after hospital discharge and lack of patient and family education during hospital stay or in postdischarge or primary care settings. As a result, low medication compliance and poor risk factor control have been reported among patients who have had a stroke in Bangladesh [18].

### Study Objectives

The objective of this study is to evaluate the effectiveness of a health education program for patients who had their first stroke (transient ischemic attack, hemorrhagic stroke, lacunar stroke, atherothrombotic stroke, or cardioembolic stroke) and their family caregivers in order to reduce the recurrence of stroke.

### Study Framework and Hypothesis

In Bangladesh, lack of patient and family education during and after hospital discharge has led to poor follow-up, including low compliance with clinical visits, medications, and lifestyle changes, resulting in negative outcomes [18]. From the nursing perspective, this study aims to reduce recurrence by fostering (self)-management skills through health education on modifiable risk factors of stroke. After patients or caregivers acquire knowledge and are aware the importance of health care management, their lifestyle behaviors can be changed. (Self)-monitoring of BP, medications, and clinical visits will enhance adherence to treatment and consequently control for the risk factors, increase QoL, and reduce stroke recurrence. Therefore, we hypothesized that health education of patients who had their first stroke and their family caregivers could reduce the stroke recurrence rate by controlling the modifiable risk factors compared to patients who did not receive health education. Health education during the hospital stay of patients who had a stroke and their continuous care after discharge are essential. Therefore, we developed a conceptual framework (Figure 1) to illustrate the factors that influence the recurrence of stroke, and we conducted postdischarge education for patients and families to prevent the recurrence of stroke for the first time in Bangladesh. The American Heart Association and Canadian guidelines recommended healthy lifestyle and management of vascular risk factors for the secondary prevention of stroke [19,20]. Meta-analyses of randomized controlled trials on intensive control of systolic BP [21,22] and improved antiplatelet therapy [23] reported significant reduction in the recurrence of stroke. Lifestyle-related behaviors such as diet, physical activity, and smoking contribute to vascular risk factors of stroke; however, there is knowledge gap on if modifying these behaviors significantly reduce stroke recurrence in stroke survivors [19]. Moreover, there is evidence that positive lifestyle change in intervention studies focused on improving recurrence prevention behaviors [17], but it is not established if lifestyle changes can reduce stroke recurrence. Patients’ medication adherence can be improved by providing information regarding the advantage of taking treatments, reminders, and (self)-monitoring [24]. Moreover, the (self)-management behavior of patients who had a stroke improved their self-efficacy, disease outcome, QoL, and self-satisfaction that could improve stroke recurrence [25]. It also increased patients’ self-confidence and well-being [26].

**Figure 1 figure1:**
[figure not shown]
Conceptual framwork.

To enhance the knowledge and awareness of modifiable risk factors, we provided health education on various topics: (1) diet (reducing salt intake, maintaining a balanced diet, and managing weight) (Multimedia Appendix 1), (2) physical activity (increasing exercise or rehabilitation if patients are bedridden) (Multimedia Appendix 2), (3) smoking cessation and reducing alcohol consumption (Multimedia Appendix 3), (4) medication compliance and regular clinical visits (Multimedia Appendix 4), and (5) (self)-monitoring of BP (caregivers monitor BP if patients are unable to do so themselves) (Multimedia Appendix 5). Additionally, patients are educated about the importance of taking medication as prescribed and recognizing stroke symptoms. In Bangladesh, where the illiteracy rate is still high [27], the investigators developed an easy-to-understand study book named “Preventing Recurrence of Stroke: Friendly Health Education Booklet,” featuring illustrations and photos tailored to Bangladeshi culture and lifestyle. Based on the study book, videos were produced to ensure that even illiterate patients and caregivers could understand the content and watch them repeatedly. Furthermore, a 45-minute hands-on training session is provided for better comprehension. To ensure adherence to these (self)-management activities, the investigators provide patients with a digital BP machine, a salt-measuring spoon, and a medication box that divides the medicines for 1 week into morning, afternoon, evening, and bedtime doses. These tools are accompanied by a health education booklet and video, as well as a (self)-monitoring notebook for patients to utilize at home. The (self)-monitoring notebook is designed for patients or family caregivers to record daily monitoring data, including medication, BP readings, and any notable observations for a duration of 12 months. Nurses regularly contact patients to ensure they are measuring and recording data correctly, explaining how to interpret BP readings and their implications. The investigators recognize the critical importance of daily (self)-monitoring of BP to promote awareness of the patients’ condition and foster a sense of (self)-management. In Bangladesh, where the practice of measuring BP at home or even in hospitals is rare, investigators teach patients and caregivers how to measure BP, which is a new concept for the population who have never measured their BP levels before [28]. Another significant aspect is monitoring salt intake. The average daily salt consumption among Bangladeshi people ranges between 15 g/day and 21 g/day [29]. Due to the scarcity of processed and packaged foods in Bangladesh, where salt is the main seasoning, the concept of “measuring salt” is uncommon. Education on low-salt diets is virtually nonexistent in the country. Hence, it is crucial to teach individuals to comprehend and visualize “5 g of salt” by using a measuring spoon. Additionally, physical activities will be taught by a physical therapist.

## Methods

### Study Design

This is an ongoing 12-month intervention study. This study follows a parallel (1:1), open-label, prospective, randomized controlled trial design, and adheres to the CONSORT (Consolidated Standards of Reporting Trials) guidelines [30]. The study flowchart is depicted in Figure 2. This study commenced in October 2022 and is expected to conclude in March 2024, with a total duration of 18 months. This trial is registered as ClinicalTrials.gov NCT05520034.

**Figure 2 figure2:**
[figure not shown]
CONSORT (Consolidated Standards of Reporting Trials) chart.

### Study Site, Population, and Sample

This study was conducted at the National Institute of Neurosciences & Hospital (NINS&H) in Dhaka, Bangladesh. NINS&H is a state-run tertiary care hospital in Bangladesh that treats patients with neurological disorders. The inclusion criteria for enrollment encompassed individuals who experienced their first stroke attack, regardless of whether it was the ischemic or hemorrhagic subtype. In Bangladesh, ischemic stroke accounts for over three-quarters of cases [4], and health education can be effective for patients with ischemic stroke classified as modified Rankin Scale (mRS) scores 0-2. For hemorrhagic stroke, considering the impact of self-management, patients with an mRS score below 3 were included. However, in the context of Bangladesh, family caregivers often provide care, and if family education is considered, patients with an mRS score of 4 were also included. Additionally, we included patients who have an mRS score of 0-4, were 18 years of age or older, and of any gender. Moreover, due to the limited availability of emergency hospital beds in Bangladesh, patients with an mRS score of 0-2, particularly those with lacunar infarcts, are often treated as outpatients. Hence, we included outpatient care in our study. In cases where patients were unable to care for themselves and relied on the support of family caregivers, consent was obtained from the caregivers. Primary caregivers, regardless of gender, who were 18 years of age or older, and resided with the patients were recruited. The exclusion criteria consisted of patients with a history of stroke recurrence, stroke caused by genetic factors or injury or accident, multiorgan failure, terminal illness, or previous participation in other clinical trials. Patients with an mRS score of 5, indicating severe disability requiring constant nursing care, were excluded [31]. In such cases, health education and follow-up may not have a significant impact. Additionally, individuals younger than 18 years, mentally unstable, cognitively impaired (diagnosed cases), and family caregivers who did not reside with their patients were also excluded from this study. When patients were admitted as inpatients or visited the outpatient department of the hospital, investigators and the research assistant (RA) nurses reviewed the participants’ admission or visiting files, including their current medications. Subsequently, the RA nurses visited the inpatient wards and brought the outpatients to a designated research room within the hospital.

### Patient Enrollment

A total of 760 patients were screened, and among them, 432 patients were enrolled. We randomly allocated 216 patients to the intervention group and 216 patients to the control group. After completion of 12 months follow-up, we will analyze the data.

### Randomization Schedule

A randomization schedule was used following the stratified randomization technique on a computer-generated series of numbers. On the basis of studies conducted in China [32,33], we stratified the patients into <65 years group and ≥65 years group, as the study site had no statistics about the age of the patients with recurrent stroke and types of strokes (hemorrhagic stroke, large artery atherosclerosis, cardioembolic, small vessel occlusion, lacunar, transient ischemic attack) because recurrence rates differed by the stroke type [6]. An experienced investigator who was not involved in this study generated the random allocation number by sequences. She distributed them in sealed opaque envelopes with serial numbers, which were kept in locked file cabinets in the hospital.

### Study Procedure

Enrollment occurred over a span of 6 consecutive days during morning hours, excluding government holidays, within a week. After determining eligibility and obtaining consent, the RA nurses opened the sealed randomization envelope in the presence of the participants. They collected demographic information, conducted physical examinations, and filled up questionnaires (Table 1).

**Table 1 table1:** Study activities.

Schedule	Intervention group	Control group
At baseline	Data collection by RA^a^ nurses through structured questionnaires RA nurses provide knowledge-related health education before discharge or after the hospital visit: health education (face-to-face, 45 min) by RA nurse and exercise session by the physiotherapist RA nurses perform physical examination: BP^b^ level (systolic and diastolic) Blood tests: HbA_1c_^c^, total cholesterol, and HDL cholesterol (calculate non-HDL cholesterol)	Data collection by RA nurses through structured questionnaires Provide usual practice RA nurses perform physical examination: BP level (systolic and diastolic) Blood tests: HbA_1c_, total cholesterol, and HDL^d^-cholesterol (calculate non-HDL cholesterol)
Middle of study (6 months)	Data collection by RA nurses through structured questionnaires RA nurses provide refresher health education same as baseline RA nurses perform physical examination: BP level (systolic and diastolic) Blood tests: HbA_1c_, total cholesterol, and HDL cholesterol (calculate non-HDL cholesterol)	Data collection by RA nurses through structured questionnaires Provide usual practice RA nurses perform physical examination: BP level (systolic and diastolic) Blood tests: HbA_1c_, total cholesterol, and HDL cholesterol (calculate non-HDL cholesterol)
End of study (12 months)	Data will be collected by RA nurses through structured questionnaires RA nurses will perform physical examination: BP level (systolic and diastolic) Laboratory tests: HbA_1c_, total cholesterol, and HDL cholesterol (calculate non-HDL cholesterol)	Data will be collected by RA nurses through structured questionnaires RA nurses will provide health education at the end of the study, and a health education booklet will be given to them RA nurses will perform physical examination: BP value (systolic and diastolic) Laboratory tests: HbA_1c_, total cholesterol, and HDL cholesterol (calculate non-HDL cholesterol)

^a^RA: research assistant.

^b^BP: blood pressure.

^c^HbA_1c_: glycated hemoglobin.

^d^HDL: high-density lipoprotein.

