### Intervention Group Study Plan

After obtaining informed consent and baseline data, RA nurses provide health education through a booklet to patients and family caregivers and give them the booklet to follow the instructions at home. Subsequently, a video containing the risk factors of stroke and their management and prevention is shown to the patients and family caregivers. Health education sessions on booklet contents take around 20 minutes, and video show sessions take around 15 minutes. We provide these health education sessions 2 times after enrollment of the patients and 6 months after the follow-up visit in the hospital. Health education booklets guide patients on how to read food labels accurately for the prevention of stroke-related risk factors. Booklets have a reminder for the schedule date of the next clinic visits. There is also a notebook for recording daily health monitoring charts such as BP, exercise, and medication intake by the patients or caregivers. The video presentation includes simulation training on essential tasks such as how to measure BP and organize the medication boxes prescribed by physicians. We recommended placing the medications in our provided medication boxes to increase the adherence to doctors’ guidelines for consumption and using salt-measuring spoons. After that, an assigned physiotherapist provides about 15-minute exercise orientation sessions to show how to do physical exercises at home. A repeated session is conducted by the physicians and RA nurses at 6-month follow-ups for their memorization. RA nurses provide motivational SMS texts every month to the patients and caregivers to remind patients to measure their daily BP, reduce salt intake, avoid oily and fatty foods, consume more fruits and vegetables, exercise regularly, and adhere to their medication regimen. Additionally, RA nurses provide refresher health education twice a month in the first 3 months and then monthly in the next 9 months over a phone call to obtain information about the health condition of the patients and document in the questionnaires. Patients receive a reminder phone call on the fifth month to visit the hospital for the sixth month follow-up visit. At the 6-month follow-up visit (middle of study), if the patient and family caregiver are not able to come for any reason, RA nurses collect data and provide refresher health education over a phone call (Figure 3).

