### Study Preparation

#### Training of RA Nurses

Five RA nurses were recruited from NINS&H and another tertiary hospital, and 5 student nurses were recruited from 2 nursing schools for this study. Investigators provided protocol-specific theoretical and practical training to all RA nurses before the study initiation. They received training on physical measurements and were taught the motivational interviewing technique [36] to effectively encourage patients who had a stroke to adhere to instructions. We trained them how to educate patients to maintain daily activities and to send SMS text messages. Throughout the study, the RA nurses have been receiving monthly feedback sessions on the participants’ health education materials.

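### The RA-nurse role both delivers the education and collects the 6- and 12-month questionnaires and BP, with no stated separation, which exposes the self-reported secondary outcomes to bias

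*Protocol article*

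**What the plan says.** All references are to the protocol article.

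- **Design.** Under Study Design: "This study follows a parallel (1:1), open-label, prospective, randomized controlled trial design".
- **Allocation.** Under Study Procedure, "the RA nurses opened the sealed randomization envelope in the presence of the participants". The role therefore knows the arm from the start.
- **Delivery.** RA nurses give the baseline session. At 6 months, according to Table 1, "RA nurses provide refresher health education same as baseline". Under Intervention Group Study Plan, "RA nurses provide motivational SMS texts every month to the patients and caregivers", and by telephone "RA nurses provide refresher health education twice a month in the first 3 months and then monthly in the next 9 months". These calls also gather health information for the questionnaires.
- **Assessment.** Table 1 gives RA nurses the questionnaires and BP in both arms at baseline, 6 and 12 months. For 12 months it states "Data will be collected by RA nurses through structured questionnaires" and "RA nurses will perform physical examination: BP level (systolic and diastolic". Under Data Monitoring and Quality Assurance, RA nurses also complete the forms and enter the data.
- **Combined contact.** If an intervention patient cannot attend at 6 months, the Intervention Group Study Plan has RA nurses collect the data and give the refresher in a single telephone call.
- **Staff.** Under Training of RA Nurses: "Five RA nurses were recruited from NINS&H and another tertiary hospital, and 5 student nurses were recruited from 2 nursing schools". No division into educators and assessors is given.

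**The concern.** Lifestyle behaviour, medication adherence and QoL are reported by the patient to a nurse. The first two ask about the behaviour that the intervention urges: diet, salt, exercise, taking medicines. A patient who has been taught and reminded of these by the nursing team has reason to give that team the desired answer. A nurse who knows the arm and has worked to change the behaviour may prompt or record generously. Control patients have not been taught the content, so this part of the bias differs between arms and would look like a treatment effect.

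The stake is more than descriptive. The Conclusions section names a significant QoL improvement as grounds for introducing the program into the national health care system. The Limitations section mentions differing levels of understanding and baseline heterogeneity, but not this overlap.

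**Working it through.** **Step 1: who does what, by role.**

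| Task | Role named | Place |
|---|---|---|
| Opens envelope | RA nurses | Study Procedure |
| Teaches at baseline and 6 months | RA nurses (with physiotherapist; physicians also at 6 months) | Table 1; Intervention Group Study Plan |
| Texts and education calls | RA nurses | Intervention Group Study Plan |
| Questionnaires and BP at 6 and 12 months | RA nurses | Table 1 |
| Confirms recurrent stroke | Treating physician | Operational Definitions |

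The overlap is stated by role. The assignment of individual nurses to individual patients is not described.

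**Step 2: contact by arm.** Intervention: 2 calls × 3 months + 1 call × 9 months = 15 education calls. Control: one call a month for a year = 12 calls, for information only. Both arms get to know the nurses, but only one arm is taught.

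**Step 3: number per arm.** The Sample Size section uses 0.10 against 0.20, two-sided 5% and 80% power:

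(1.96 + 0.84)² × (0.10 × 0.90 + 0.20 × 0.80) / 0.10² = 7.84 × 0.25 / 0.01 = 196 per arm, as stated.

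196 × 1.10 = 215.6, so 216 per arm, as stated. These figures are not in dispute. With the planned 10% loss, 216 × 0.90 ≈ 194 per arm have 12-month data.

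**Step 4: what a given shift would do.** Take a score with no true effect, compared between arms by a two-sided 5% test. In SD units the standard error of the difference is √(2/n). With shift b, the rejection probability is 1 − Φ(1.96 − b/SE) + Φ(−1.96 − b/SE).

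For n = 194, SE = √(2/194) = 0.1015.

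| Assumed shift (SD) | b/SE | Rejection, 194 per arm | Rejection, 216 per arm |
|---|---|---|---|
| 0 | 0 | 5.0% | 5.0% |
| 0.1 | 0.985 | 16.6% | 18.0% |
| 0.2 | 1.970 | 50.4% | 54.7% |

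A shift of 1.96 × 0.1015 = 0.199 SD would by itself bring the expected z to 1.96. The shift sizes are assumptions, because the article gives no SD for any scale.

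**Step 5: what a new assessor could recover.** Participants know that they were educated, so some of the shift would remain whoever asks. If a 0.2 SD shift were halved to 0.1 SD (again an assumption), the table gives a fall from about 50% to about 17%, not to 5%.

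**The case against.** - **The overlap is documented by role only.** A reader might infer that every patient is questioned by the nurse who taught that patient, who is then judging her own work. The article does not say so, and a full protocol could hold a roster. This objection stands against the person-level reading. It does not remove the point, because the article assigns both tasks to one unblinded role and makes the 6-month telephone fallback a single contact for both.
- **The bias is not all in one arm.** A reader might infer that only intervention patients are affected. Control patients also speak to RA nurses monthly and are assessed by the same role, so general courtesy can operate in both arms. Only the part tied to taught content is differential.
- **The outcomes differ in exposure.** A reader might extend the point to every end point. Knowledge items have right and wrong answers, and giving the taught answer is largely the intended effect. BP is a measurement, and the device used at visits is not stated. HbA1c and non-HDL cholesterol are laboratory values. The primary end point is confirmed by the treating physician. This objection stands.
- **There is a quality check.** Investigators check 5% of participants' data on the same day, and review data collection and examination. It is a small safeguard, not described as blinded, and it is aimed at errors rather than at reporting bias.
- **The magnitude is hypothetical.** True. The calculation shows how small a shift would matter at this sample size, not that one exists.

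**Conclusion.** The point holds at the level of staff role. In an open-label design, the RA nurses who open the allocation and deliver the education, texts and 15 calls also administer the questionnaires and BP at 6 and 12 months, and no separation is stated. The exposure is mainly in self-reported lifestyle, medication adherence and QoL. It is less for knowledge and BP. The laboratory values and the primary end point are not covered.

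If the differential shift were 0.1 to 0.2 SD, the false-positive rate for a scale with no true effect would be about 17% to 50% with 194 per arm. That rests on an assumed shift and the planned 10% loss, and only part of it is avoidable. The point merits a change because the remedy is cheap and QoL is named as a basis for adoption. It does not invalidate the trial.

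**What to change.** **Remaining 12-month visits.** Roster the trained RA nurses so that each participant's questionnaires and BP are done by a nurse who did not enrol, educate or call that participant and is not told the arm. Do this before any end-of-study education of control participants, which Table 1 also gives to RA nurses. Record the assessor's identity, and whether that nurse had earlier contact, for a sensitivity analysis.

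**Assessments already done.** Enrolment ran from October 2022 to February 2023, so the 6-month visits and perhaps many 12-month visits may be past. For these, state the overlap as a limitation, and interpret the self-reported outcomes beside HbA1c and non-HDL cholesterol.

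**Cost.** No extra visits, and no extra staff if the five RA nurses suffice. The article states training for the RA nurses; the role and training of the student nurses are less clear, so the roster should not depend on them. Scheduling becomes somewhat harder. If calls were shared among all the nurses, some participants may have no uninvolved nurse left. Masking will be imperfect, because patients may reveal what they were taught. The assessor would change between 6 and 12 months, which affects comparability over time in the repeated-measures analyses, but the change applies equally to both arms.
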